1

2

## 2 Abbreviations and Definitions

|         |                                                |
|---------|------------------------------------------------|
| ITM     | Intrathecal Morphine                           |
| TAPB    | Transversus Abdominis Plane Block              |
| ERAS    | Enhanced Recovery After Surgery                |
| QoR-15  | Quality of Recovery-15                         |
| MME     | Morphine Milligram Equivalents                 |
| ITT     | Intention-to-treat                             |
| CONSORT | Consolidated Standards of Reporting Trials     |
| ASA     | American Society of Anesthesiologists          |
| NRS     | Numerical Rating Scale                         |
| IWRS    | Interactive Web-based Response System          |
| TCI     | Target-controlled Infusion                     |
| BIS     | Bispectral Index                               |
| NOX     | Nociception Index                              |
| PONV    | Postoperative Nausea and Vomiting              |
| PCIA    | Postoperative Controlled Intravenous Analgesia |
| PACU    | Post-anesthesia Care Unit                      |
| CRF     | Case Report Form                               |
| MICD    | Minimum Clinically Important Difference        |
| SD      | Standard Deviation (SD)                        |
| GEE     | Generalized Estimating Equation (GEE)          |
| RDs     | Rate Differences (RDs)                         |

## 3 Introduction

This document details the statistical analysis plan for Effect of Intrathecal Morphine Combined with Transversus Abdominis Plane Block on Quality of Recovery After Laparoscopic Colorectal Surgery: A Randomized Clinical Trial. The clinical trial is registered at ClinicalTrials.gov (NCT06636864). One should also refer to the trial

46 protocol paper.

47  
48  
49  
50  
51  
52  
53  
54  
55  
56  
57  
58  
59  
60  
61  
62  
63  
64  
65  
66  
67  
68  
69  
70  
71  
72  
73  
74  
75  
76

## 4 Study Objectives and Endpoints

### 4.1 Study Objectives

The aim of the study is to evaluate whether intrathecal morphine (ITM) combined with transversus abdominis plane block (TAPB) improves postoperative recovery quality after laparoscopic colorectal surgery.

### 4.2 Endpoints

#### Primary endpoint:

The primary endpoint is the QoR-15 score at 24 h postoperatively.

Definition : QoR – 15 is a scale used to assess the quality of postoperative recovery. It was developed by McDowell and his team in Sweden in 2005 and is a simplified version of the QoR scale. QoR – 15 consists of 15 items and 5 domains, namely physical state, cognitive state, emotional state, social state, and pain state. It assesses the quality of postoperative recovery by measuring the patient's self – perceived psychological and social function states. Each item is scored on a 10 – point scale, with a total score of 150 points. The higher the score, the better the recovery quality.

#### Secondary endpoints:

- 1) QoR-15 scores at 48 and 72 h postoperatively,
- 2) cumulative opioid consumption (MME) at 24, 48, and 72 h postoperatively,
- 3) total intraoperative opioid dosage,
- 4) NRS scores during rest or movement in the post-anesthesia care unit (PACU) or at 24, 48, and 72 h postoperatively,
- 5) time to first flatus,
- 6) time to first ambulation,
- 7) supplementary analgesic dosage at 24, 48, and 72 h postoperatively,
- 8) adverse events (dizziness/headache, nausea/vomiting, pruritus, hypotension) at 24, 48, and 72 h postoperatively and
- 9) length of hospital stay.

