## 5.3 Randomization and Blinding

Potential trial participants were identified by a research team member through electronic medical record screening. Eligible patients were approached, and written informed consent was obtained either before surgery. Patients were randomly allocated in a 1:1 ratio to receive either the intervention group or the control group using Sun Yat–sen University Cancer Center' s (SYSUCC) interactive web–based response system (IWRS). Allocation concealment was ensured by restricting researcher access to the randomization system until study completion. An independent research assistant conducted randomization using sequentially numbered, opaque envelopes containing group assignments. Based on group assignments, the pharmacist prepared identical 5 mL intrathecal solutions (normal saline or morphine) in 10 mL syringes for administration. To ensure blinding, the administering anesthesiologist was excluded from subsequent procedures and data collection. An independent researcher, blinded to group allocation and uninvolved in interventions or analysis, collected all outcome data.

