## 6 Sample Size

The primary outcome measure was the QoR-15 score at 24 h postoperatively. Based on previous literature and the results of pilot experiments, the minimum clinically important difference (MICD) of the QoR-15 score was determined to be 6.0. The standard deviation (SD) of the QoR-15 score after major surgery ranged from 10 to 16. Taking a conservative estimate, we selected an SD of 16. Assuming  $\alpha = 0.05$  and  $\beta = 0.2$  (with a power of 80% to detect this difference), calculations were performed using PASS 21 software. The result indicated that 113 patients were required in each group. Considering a 10% dropout rate, our target was a final sample size of 252.

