## 198 9 Efficacy Analyses

199 This analysis adhered to the intention-to-treat (ITT) and per-protocol principle.  
200 Continuous quantitative data were described as mean  $\pm$  standard deviation if  
201 normally distributed, with between-group comparisons performed using  
202 independent t-tests. Non-normally distributed data were summarized as median  
203 (P25, P75) and analyzed using the Wilcoxon rank-sum test. Categorical variables  
204 were expressed as frequencies (percentages), with group comparisons conducted  
205 via Chi-square tests or Fisher's exact test, as appropriate. Ordinal data were  
206 similarly described as frequencies (%) and compared using the rank-sum test.

207 For the primary outcome, intergroup differences were assessed using a generalized  
208 estimating equation (GEE) model implemented via the R package geepack, with an  
209 exchangeable correlation structure. The model incorporated time, group, their  
210 interaction (time  $\times$  group), and adjustments for age, sex, weight, ASA classification,  
211 complications, anesthesia duration, and baseline values. Estimated marginal means  
212 at each time point were visualized using line plots, either as absolute values or  
213 relative changes from baseline.

214 Binary outcomes were reported as counts (%) and analyzed using generalized linear  
215 models to estimate rate differences (RDs) with 95% CI, adjusting for age, sex,  
216 weight, ASA status, complications, and anesthesia duration. For ordinal outcomes,  
217 between-group comparisons employed the rank-sum test, with median differences  
218 and 95% CI calculated. Single-measurement continuous outcomes were analyzed via

219 linear regression, adjusting for the same covariates.

220 Longitudinal outcomes lacking baseline measurements were evaluated using GEE  
221 models (exchangeable correlation) with time, group, their interaction, and  
222 covariates (age, sex, weight, ASA, complications, anesthesia duration). Estimated  
223 trends were plotted by group. All analyses and visualizations were performed in R  
224 (v4.4.1).

225 Results of efficacy analyses will be presented as tables or in text in the final  
226 publication(s), including p-values.

227 9.1 Primary Efficacy Analysis

228 Analysis of primary endpoint (xx) will be performed in accordance with section 9.

229 9.2 Secondary Efficacy Analyses

230 Analyses of secondary endpoints will be performed in accordance with section 9.

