231 9.3 Exploratory Efficacy Analyses

232 Further analysis of exploratory analyses will be performed in accordance with  
233 section 9.

234

235 10 Safety Analyses

236 All adverse events which are directly connected to study procedures will be  
237 documented and reported by appropriate statistical methods in accordance with  
238 section 9.

239

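### Secondary endpoint 8 schedules only four adverse-event items, so other opioid-type harms of intrathecal morphine reach the comparison only by attribution under section 10, and a combined dizziness/headache item hides which symptom differs

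*SAP*

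**What the plan says.** SAP section 4.2, secondary endpoint 8, reads "adverse events (dizziness/headache, nausea/vomiting, pruritus, hypotension) at 24, 48, and 72 h postoperatively". The bracket holds four items, two of them combinations. No wording marks them as examples. Respiratory depression, sedation and urinary retention are named nowhere in the SAP.

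Section 5.3 fixes the contrast: "the pharmacist prepared identical 5 mL intrathecal solutions (normal saline or morphine) in 10 mL syringes for administration". Both arms therefore have an intrathecal injection, and they differ in whether it contains morphine.

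Section 10 has a different scope. It begins "All adverse events which are directly connected to study procedures will be" and goes on to say that these events are documented and reported by the methods of section 9. Section 9 says "Binary outcomes were reported as counts (%) and analyzed using generalized linear" models, which give adjusted rate differences with 95% confidence intervals.

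**The concern.** The listed items are prespecified for assessment at fixed times, which implies that every patient is assessed for them. An unlisted event reaches the analysis by another route: someone has to notice it, record it and attribute it to a study procedure. The SAP gives no criterion for that attribution, names no assessor, and does not say that unlisted events are compared between arms. After general anesthesia and colorectal surgery, drowsiness, a low respiratory rate or a bladder problem is easily put down to something else. An event with a plausible competing explanation is the kind that an attribution filter loses.

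The second issue is the combined dizziness/headache item. Headache can follow the dural puncture, which both arms have. Dizziness can be an opioid effect, which would differ by arm. A single combined rate cannot show which of the two moved.

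At stake is the safety statement that accompanies the efficacy result. A table limited to the four items could be read as a general assurance about intrathecal morphine, when it speaks to only part of the relevant harms.

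**Working it through.** **1. The two scopes side by side**

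| | Endpoint 8 (section 4.2) | Section 10 |
|---|---|---|
| Which events | Four named items | Any event tied to study procedures |
| When | 24, 48 and 72 h | Not stated |
| Depends on attribution | No | Yes; criterion and assessor not stated |
| Compared between arms | Yes, by the section 9 rate difference | Section 9 methods, but a between-arm comparison of unlisted events is not stated |

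The three unlisted harms fall only in the right-hand column.

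**2. The plan's own sample size**

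Inputs from section 6: "MICD) of the QoR-15 score was determined to be 6.0", "Taking a conservative estimate, we selected an SD of 16", two-sided alpha 0.05, power 80%. Allocation is 1:1 (section 5.3).

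- n per group = 2 × (1.960 + 0.842)² × 16² / 6² = 111.6, so 112 by the normal approximation. The t-test version gives 112.6, so 113.
- With 10% dropout, 113 / 0.9 = 125.6, so 126 per group and 252 in total.

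The stated 113 and 252 reproduce. The checks below use 113 per arm.

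**3. Effect of combining dizziness and headache**

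The SAP gives no adverse-event rates, so all rates here are assumptions. With independent symptoms, the combined rate = 1 − (1 − dizziness)(1 − headache). Power = Φ(difference / SE − 1.96), with SE = √{[p₁(1 − p₁) + p₂(1 − p₂)] / 113}.

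Dizziness is set at 10% (saline) vs 20% (morphine), and headache is equal in both arms:

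| Headache, both arms | Rates compared | Difference | SE | Power |
|---|---|---|---|---|
| Dizziness alone | 10.0% vs 20.0% | 10.0 points | 0.0470 | 57% |
| 5% | 14.5% vs 24.0% | 9.5 points | 0.0521 | 45% |
| 10% | 19.0% vs 28.0% | 9.0 points | 0.0561 | 36% |
| 20% | 28.0% vs 36.0% | 8.0 points | 0.0618 | 25% |

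The reverse case has both symptoms rising with morphine: dizziness 10% vs 20% and headache 5% vs 15%.

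- Combined rates: 1 − 0.90 × 0.95 = 14.5% and 1 − 0.80 × 0.85 = 32.0%.
- Power is about 89% for the combined item, against 57% for dizziness and 72% for headache. Using the pooled variance under the null instead gives 88%, 56% and 71%.

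So combining lowers power when one component differs and can raise it when both do.

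**4. What listing rare harms would and would not give**

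- Chance of at least one event in 113 patients = 1 − (1 − p)¹¹³. This is 43%, 68% and 90% for assumed true rates of 0.5%, 1% and 2%.
- Zero events in 113 patients gives an upper 95% bound of about 3/113 = 2.7%, which is valid only if every patient was assessed.
- Power is about 19% for 1% vs 3%, and 23% for 2% vs 5%.

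Listing the items would secure complete capture and an honest interval. It would not give a powered test.

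**The case against.** The strongest reply is that section 10 already covers these harms. An episode of respiratory depression or urinary retention judged related to the intrathecal injection would be documented and reported by section 9 methods. This stands. A reader might infer from endpoint 8 that the three harms are not collected, are never compared, or have nowhere to be recorded. The SAP does not support that reading: being absent from a secondary endpoint is not being absent from the safety analysis. In addition, the protocol and case report form, which commonly set how adverse events are collected, are not at hand.

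A second reply is that the SAP nowhere calls these three events expected harms. That is also true. The premise is general knowledge of opioids, stated here as an assumption, and no figure above depends on it.

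A third reply concerns dilution. A reader might infer that the combined item necessarily weakens the safety comparison. It does not, as the reverse case shows. Nor does the SAP rule out tabulating the components separately; it is silent on this.

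Finally, the added items would be underpowered if rare. Agreed: the gain is in ascertainment and reporting.

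What these replies leave standing is the reliance on an undefined attribution step in place of scheduled assessment, and the loss of information about which symptom differs.

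**Conclusion.** The point holds as one about scope and ascertainment. Endpoint 8 prespecifies scheduled comparison of four items. Other opioid-type harms of the randomized treatment enter only through section 10, on an attribution judgement that the SAP does not define, so their capture is likely to be less complete. How much would be missed cannot be calculated from the document.

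For the combined item, the loss of interpretability is certain unless the components are also tabulated. The effect on power can go either way: from about 57% down to 45%, 36% or 25% in the one-sided scenarios, or up to about 89% where both symptoms rise. These figures assume independent symptoms, 113 per arm and rates that the SAP does not give.

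This is an inexpensive improvement worth making. It does not invalidate the planned safety analysis.

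**What to change.** - Extend endpoint 8 to respiratory depression or desaturation, over-sedation, and urinary retention. Define each item, and extract it for every patient from routine records over 0-72 h, blind to allocation and regardless of attributed cause. This remains possible if patients have already been followed up, provided that the records hold the information.
- Report dizziness and headache as separate items alongside the combined one.
- Analyse each item by the section 9 rate difference with a 95% confidence interval.
- Make section 10 consistent with this scope: state how connection to study procedures is judged, by whom and blind to allocation, and whether unlisted events are compared between arms.

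The cost is a few more data fields and table rows. Intervals for rare events will be wide, and those comparisons should be described as unpowered. No change to patient management is proposed.

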## 5 Study Methods

### 5.1 General Study Design and Plan

This single-center, prospective, randomized, double-blind, placebo-controlled trial was conducted at the Sun Yat-sen University Cancer Center. All participants provided written informed consent prior to participation. Ethical approval for the study (B2024-514-01) was granted by the Ethics Committee of Sun Yat-sen University Cancer Center. The trial was prospectively registered on ClinicalTrials.gov on October 15, 2024 (NCT06636864, <https://clinicaltrials.gov/study/NCT06636864>, principal investigator: [name]) prior to patient enrollment. The first case was enrolled on October 16, 2024. The study adhered to the Consolidated Standards of Reporting Trials (CONSORT) guidelines and was conducted in compliance with the ethical principles outlined in the Declaration of Helsinki and its subsequent amendment.

| Timepoint                              | Study Period       |                |                 |              |              |              |                         |                                       |
|----------------------------------------|--------------------|----------------|-----------------|--------------|--------------|--------------|-------------------------|---------------------------------------|
|                                        | Enrolment          | Allocation     | Post-allocation |              |              |              | Close-out               |                                       |
|                                        | Day before surgery | Day of surgery | PACU            | Post op Day1 | Post op Day2 | Post op Day3 | Length of hospital stay | Length of hospital stay after surgery |
| ENROLMENT                              |                    |                |                 |              |              |              |                         |                                       |
| Eligibility screen                     | ×                  |                |                 |              |              |              |                         |                                       |
| Informed consent                       | ×                  |                |                 |              |              |              |                         |                                       |
| Medical history taking                 | ×                  |                |                 |              |              |              |                         |                                       |
| Allocation                             |                    | ×              |                 |              |              |              |                         |                                       |
| INTERVENTIONS                          |                    |                |                 |              |              |              |                         |                                       |
| Intrathecal morphine or salute         |                    | ×              |                 |              |              |              |                         |                                       |
| Transversus abdominis plane block      |                    | ×              |                 |              |              |              |                         |                                       |
| ASSESSMENTS                            |                    |                |                 |              |              |              |                         |                                       |
| QoR-15 scores                          | ×                  |                |                 | ×            |              | ×            |                         |                                       |
| NRS                                    |                    |                | ×               | ×            |              | ×            |                         |                                       |
| Total opioid consumption               |                    |                |                 | ×            |              | ×            |                         |                                       |
| Time of the first flatus               |                    |                |                 |              | ×            |              |                         |                                       |
| Time of the first ambulation           |                    |                |                 |              | ×            |              |                         |                                       |
| Amount of analgesic drugs supplemented |                    |                | ×               | ×            |              | ×            |                         |                                       |
| Adverse events                         |                    |                |                 | ×            |              | ×            |                         |                                       |
| Length of hospital stay                |                    |                |                 |              |              |              | ×                       | ×                                     |

Fig. 2 Time schedule of enrolment, interventions, assessments and visits for participants

## 5.2 Inclusion–Exclusion Criteria and General Study Population

### Inclusion criteria:

Patients will be included if they had:(1) were scheduled for laparoscopic colorectal surgery, (2) provided consent for combined postoperative analgesia, (3) had an American Society of Anesthesiologists (ASA) physical status classification of I to III, and (4) were aged  $\geq 18$  years.

### Exclusion criteria:

Patients will be excluded if they had:(1) declined surgery due to unforeseen circumstances or personal preference preoperatively, (2) had neurological dysfunction, (3) had contraindications to lumbar puncture, (4) had a history of preoperative opioid use, (5) reported baseline pain (assessed via the numerical rating scale [NRS]) with a score  $>3$ , or (6) required conversion to open surgery or secondary operation.

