### 7.2 Analysis Populations

Analysis will be performed 'Intention-to-treat'. All randomized subjects will be included in the final analysis.

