### 7.4 Missing Data

The missing values in Full Analysis Set will not be imputed.

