### 7.6 Confidence Intervals and p-values

All estimates of differences between groups would be presented with two-sided 95% confidence intervals unless otherwise stated. Statistical significance will be considered if  $p < 0.05$  (two-sided).

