## 8.1 Protocol Deviations

Major deviations are defined as follows:

- Wrong treatment in contrast to randomization.
- Violation of inclusion and exclusion criteria.
- Missing informed consent.

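### Exclusion criterion 6 can act for conversion to open surgery only by removing randomized patients, which contradicts SAP section 7.2, and the SAP does not settle which population decides the primary endpoint

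*SAP*

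**What the plan says.** - **Section 5.2, exclusion criteria, item 6:** patients are excluded if they "required conversion to open surgery or secondary operation".
- **Section 5.1, Fig. 2:** the eligibility screen and consent fall on the day before surgery; allocation and the intrathecal injection fall on the day of surgery. Section 5.3 agrees on consent: "written informed consent was obtained either before surgery".
- **Section 4.2, secondary endpoints:** one outcome is "total intraoperative opioid dosage", which fits treatment given before or early in the operation.
- **Section 7.2:** the analysis is by intention to treat, and "All randomized subjects will be included in the final analysis".
- **Section 7.4:** "The missing values in Full Analysis Set will not be imputed". The SAP does not define this set.
- **Section 8.1:** one type of major deviation is "Violation of inclusion and exclusion criteria". No consequence for the analysis is attached.
- **Section 9:** "This analysis adhered to the intention-to-treat (ITT) and per-protocol principle". The SAP contains no per-protocol definition, no order between the two principles, and no statement of which endpoints each applies to.

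**The concern.** An exclusion criterion should be decidable before allocation. Conversion is not: it is an event during the operation, in a patient who was eligible, consented and randomized. Applied as written, item 6 drops such a patient; section 7.2 requires the same patient to be analysed. Nothing in the SAP says which rule prevails.

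Two things are at stake. First, removing patients on an event after randomization makes the 24 h QoR-15 comparison conditional on the surgical course, so the arms compared are no longer exactly those that were randomized. Second, sections 9 and 7.4 supply two further population labels without definition or rank. Two analysts could follow this SAP, report different primary populations, and each point to supporting text. Fixing the primary population is a task for the SAP itself.

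**Working it through.** **1. The passages set side by side, for a patient converted to open surgery**

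| Step | Source | Status of the patient |
|---|---|---|
| Day before surgery | Fig. 2 | Screened and consented; conversion cannot be known |
| Day of surgery | Fig. 2 | Allocated and given the intrathecal injection |
| During surgery | Section 5.2, item 6 | Converted, so excluded |
| Analysis | Section 7.2 | Randomized, so included |
| Analysis | Section 9 | Included under ITT; undetermined under an undefined per-protocol principle |
| Analysis | Section 7.4 | Undetermined; Full Analysis Set is not defined |

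Fig. 2 gives the day, not the hour, of allocation. That allocation precedes conversion is inferred from the design: the trial treatment is meant to affect an intraoperative outcome, so it must be assigned before or early in the operation.

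**2. The SAP's sample size (section 6)**

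Inputs from section 6: difference 6.0, SD 16, alpha 0.05, power 80%, dropout 10%. Two-sided testing is from section 7.6 and 1:1 allocation from section 5.3.

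- Normal approximation: n = 2 × (1.960 + 0.842)² × 16² / 6² = 111.6, so 112 per group.
- Two-sample t-test: 112.6, so 113 per group, as stated; power at 113 is 80.1%.
- Dropout: 113 / 0.9 = 125.6, so 126 per group and 252 in total, as stated.

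The SAP's figures reproduce.

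**3. Illustration of lost patients (rates assumed; the SAP gives none)**

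Power is from the two-sample t-test with difference 6, SD 16 and two-sided 0.05.

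| Assumed removal under item 6 | Beyond the 10% dropout | Power | As the only losses | Power |
|---|---|---|---|---|
| 5% | 252 × 0.90 × 0.95 = 215, 107 per arm | 78% | 252 × 0.95 = 239, 119 per arm | 82% |
| 10% | 252 × 0.90 × 0.90 = 204, 102 per arm | 76% | 252 × 0.90 = 226, 113 per arm | 80% |

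A shortfall appears only if the removals come on top of the dropout allowance. Section 6 does not say whether conversions count as dropout.

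**4. Illustration of bias (all inputs assumed)**

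If removed patients score D points below retained patients in both arms, removing a proportion p raises an arm's mean by p × D. The between-arm difference then shifts by (p₁ − p₀) × D.

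- p₁ − p₀ = 0.05, D = 8: 0.05 × 8 = 0.4 points.
- p₁ − p₀ = 0.05, D = 16: 0.05 × 16 = 0.8 points.
- p₁ = p₀ with the same D in both arms: 0 points.

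Against the 6-point planning difference, 0.4 / 6 = 7% and 0.8 / 6 = 13%. If D differs between arms, the shift is p₁D₁ − p₀D₀, which need not be zero when the rates are equal.

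**The case against.** The strongest reply is that section 7.2 is the section that fixes the analysis population, that it names ITT alone, and that the rest is loose wording. Several parts of this reply stand, and they rule out stronger readings that a reader might draw.

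- **That naming per-protocol contradicts section 7.2.** It does not. A per-protocol analysis reported beside ITT is compatible with it. The fault in section 9 is the missing rank and definition.
- **That section 8.1 removes these patients.** It only classes criteria violations as major deviations. Read with section 7.2, such patients could be listed as deviations and still analysed.
- **That every part of item 6 is a post-randomization event.** A secondary operation is not defined and could mean an earlier or planned procedure. Conversion alone carries the point.
- **That the trial is underpowered.** The 10% allowance may already cover these patients, and the stated sample size reproduces.
- **That the treatment estimate will be biased.** Bias needs removals that differ between arms in frequency or in type of patient. The SAP describes a double-blind trial with identical syringes and gives no reason to expect conversion rates to differ. It also gives no recovery scores for converted patients.

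What the reply does not remove is the conflict itself. Item 6 is an explicit exclusion, for conversion it cannot act before allocation, and section 7.2 does not say that it overrides item 6.

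**Conclusion.** The contradiction between item 6 of section 5.2 and section 7.2 is established for conversion to open surgery, and it concerns who is in the primary analysis. It rests on the Fig. 2 schedule and on the fact that conversion is known only during surgery; it needs no assumed rate. The unranked principles in section 9 and the undefined set in section 7.4 make it worse, because they leave the population open until results are seen.

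The numerical effect is unknown from the SAP. The power of about 78% or 76% and the shift of 0.4 to 0.8 points are illustrations under assumed inputs, and neither shows that a stated figure is wrong. The point should be corrected before analysis because it is a matter of pre-specification, not because a large effect has been shown.

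**What to change.** 1. Take conversion, and any re-operation after randomization, out of the eligibility criteria and describe them as post-randomization events.
2. State what a secondary operation means. If an earlier or planned procedure is intended, word it so that it can be decided at screening.
3. Keep converted and re-operated patients in the ITT set, analysed as randomized with their available QoR-15 data.
4. State that ITT alone decides the primary endpoint. Define Full Analysis Set as that same set, or drop the term.
5. Define the per-protocol set, say how the section 8.1 deviations bear on it, and label it supportive only.
6. Tabulate conversions and re-operations by arm.

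The cost is mostly wording, and the target of 252 is unchanged. Outcome data must be kept or retrieved for a few more patients. Section 5.1 records the first enrolment on October 16, 2024, so data for patients already excluded may not all be available; their number by arm should then be reported.
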